### **13.4 Risks**

The Investigators will ensure that the dignity, rights, safety and well-being of participants are given priority at all times.

York Hospital Emergency Department will receive the protocol and information relating to the IMP prior to the study commencing and will be notified of dosing days.

The MABs C2F5, C2G12 and C4E10 have not been used intravaginally in humans, however clinical experience exists from intravenous infusions of the MABs:

In the course of 4 clinical trials the antibodies were infused intravenously to 39 human HIV-1 infected subjects. Antibodies were administered in high dose regimens using multiple repeated infusions and patients received doses up to 80 g of antibodies within a period of 16 weeks. The antibodies were extremely well tolerated in all clinical trials and few adverse events were observed. Of note, the rate of adverse events observed was not related to the dose. Laboratory safety parameters (haematology, clinical chemistry and urinalysis) showed either changes within the normal range or no change compared with pre-trial levels in most patients. Possible antibody related adverse events were primarily myalgias (n = 7) and arthralgias (n = 4). A laboratory adverse event with established relationship to the infusion of antibody C4E10 was a mild prolongation (grade 1 or below) in activated partial thromboplastin time (APTT) directly after antibody infusion in high dose. Prolongations were transient and aPTT levels returned to normal upon cessation of MAb treatment and did not lead to possible related AEs.

In this study the antibodies will be applied in a significantly lower dose (~ 1/50) compared to previous studies and therefore antibody related adverse drug reactions are extremely unlikely (section 9.1).

Possible AEs may rather originate from the dosing procedure and the gel vehicle. All vaginal microbicides can cause minor local adverse events such as vaginal discharge, vaginal spotting/bleeding, vulvo-vaginal itching or burning. Therefore such side effects may be observed during this phase 1 trial, but they are usually mild and resolve during or shortly after cessation of dosing.

Blood sampling can sometimes cause bruising and soreness of the arms, or very rarely a blockage of the vein or a small nerve injury which can cause numbness and pain. Normally these problems resolve with time. Some people may faint while blood is being drawn.

Vaginal examinations and taking cervico-vaginal samples can feel uncomfortable for some women and will be very similar to having a smear test. These procedures may sometimes cause spotting. Women may also experience some discomfort and embarrassment at providing a full sexual history and from undergoing vaginal examinations. Experienced and appropriately trained study staff will conduct the vaginal examinations and the utmost care will be taken to preserve participants' dignity at all times.

If the vaginal applicator is inserted too far it may cause a very small bruise or scratch to the cervix. The participant will probably not notice these, but they may be seen during internal examination.

### **13.5 Benefits**

Although the MAbs show potent HIV-1 neutralisation *in vitro*, this is only a phase 1 study and there will be no direct benefit to the female volunteers.

Participants will receive a thorough medical examination and genitourinary infection screen. In the event of any abnormal findings being found, participants will be advised of the best course of action and referred on to appropriate clinicians where appropriate.

Although participants will receive no direct benefit, the results of the study will provide information which will help in the development of an effective vaginal microbicide. It is hoped that people at risk of HIV infection, particularly in developing countries, will ultimately benefit from the study.

### **13.6 Reimbursement**

Participants will be compensated for their time and potential discomfort or inconvenience resulting from the study. Details of compensation are provided in section 16.

### **13.7 HIV testing**

Participants will be required to undergo HIV testing as part of the eligibility screening process. Participants will receive thorough pre-test counselling in line with normal GUM clinic practices.

## **14. REGULATORY ISSUES**

### **14.1 Required approvals**

Current regulatory frameworks for this phase I trial require that the following approvals/registrations must be obtained before commencement of the trial:

- EudraCT registration (2008-000312-32)
- Clinical Trials Authorisation (MHRA approval)
- Ethical approval from an NHS Research Ethics Committee
- Research Governance Approval from York Hospitals NHS Foundation Trust

### **14.2 GCP and GMP compliance**

The trial will be compliant with the UK Clinical Trials Regulations and all study staff will be GCP trained. The study will be monitored and audited in line with GCP requirements and all adverse events will be recorded and reported.

All trial supplies will be manufactured to EU Good Manufacturing Practice (GMP) standards, as detailed in the Investigator's Brochure and IMP Dossier.

## **15. INDEMNITY**

York Hospitals NHS Foundation Trust and the University of York will act as co-Sponsors for the project.

### **15.1 Negligent harm**

Management approval from the North and East Yorkshire R&D Alliance, on behalf of York Hospitals NHS Foundation Trust will be obtained before commencement of the study. All study personnel will either be employed by the NHS or hold an honorary contract. Therefore NHS indemnity with respect to negligent harm will apply.

### **15.2 Non-negligent harm**

Cover for non-negligent harm is not provided under normal NHS arrangements. Cover for non-negligent harm will be provided by the University of York.

## **16. FINANCE**

### **16.1 Funding**

The study is supported by a grant from the European Commission and is being carried out as part of the European Microbicide Project (EMPRO). The University of York will hold the grant on behalf of the clinical trial team.

### **16.2 Reimbursement for participants**

Remuneration for taking part in the study is as follows:

- Clinic visit requiring colposcopy and/or vaginal sample collection: £65 per visit
- Clinic visit not requiring colposcopy and/or vaginal sample collection: £35 per visit
- Gel administered at home: £10 per dose

According to the full study schedule the reimbursement would be as follows:

- Visits 1 and 3 to 6: £65 per visit
- Visit 2 (extended visit, consisting of two sampling sessions)
- Doses 2-12 administered at home: £10 per dose

A participant who completes the study in full will therefore receive £565. Payment will generally be provided at the end of the trial, in the form of a cheque, unless there is good reason to do otherwise.

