## **8.7 Measures of compliance and adherence**

Compliance/adherence will be assessed by history and by inspection of returned syringes. An Investigator will assess whether the syringe is fully or partially emptied or not emptied at all. This data will be recorded in the participant's file.

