### **9.4.1 Interruption of dosing**

Interruption of dosing describes a temporary cessation of study gel use. Interruption of dosing will occur in the presence of:

- a grade 2 or above solicited genital adverse event
- any clinical event at the discretion of the CI which should lead to discontinuation of study gel

Dosing may be recommenced after interruption following an adverse event at the discretion of the CI.

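### Section 16.2 pays £10 per home dose used, so on its wording a woman whose genital symptoms lead to gel being withheld under 9.4 loses money for reporting them

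*Protocol*

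**What the plan says.** Section 16.2 sets a rate of "Gel administered at home: £10 per dose" and applies it as "Doses 2-12 administered at home: £10 per dose". The remaining items are "Visits 1 and 3 to 6: £65 per visit" and "Visit 2 (extended visit, consisting of two sampling sessions"), the latter with no amount shown. The section concludes: "A participant who completes the study in full will therefore receive £565". It adds: "Payment will generally be provided at the end of the trial". It does not say what is paid for a dose that study staff withhold.

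Section 9.4.1 makes interruption mandatory for "a grade 2 or above solicited genital adverse event". Interruption is defined as temporary, and the Chief Investigator may allow dosing to restart. Section 9.4.2 makes permanent discontinuation mandatory for a grade 3 or above solicited genital event, or a grade 3 or above clinical or laboratory event. It asks women who stop gel to keep attending follow-up where possible.

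Appendix 6 supplies the grades. Genital discomfort is graded on tolerability, awareness and control of symptoms. Non-menstrual bleeding is graded on heaviness and duration. Erythema at grades 2 and 3 combines an observed sign with the woman's discomfort grade.

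**The concern.** The event that triggers withholding of gel is, for discomfort and bleeding, something the woman herself reports. If pay follows doses used, the same report reduces her pay. The incentive is to describe a symptom as one grade milder, or not to mention it.

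Three things in the protocol depend on that report:

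- the comparisons of adverse events in section 10.2.2, which cover all adverse events as well as grade 3 or above genital events;
- the grade assigned to erythema, and through it the grade 3 or above genital endpoint in section 5.5.2;
- the rule in section 9.5 that halts the study for unblinded review once three women have a grade 3 or above event.

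This is the first vaginal use of these antibodies in humans, in 30 women randomised 1:1:1, so about 10 per arm. With so few women, absolute event counts carry much of the local safety message.

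**Working it through.** **1. Reproduce the total in 16.2.** Inputs: £65 per listed visit, £10 per home dose, doses 2 to 12, total £565.

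- Visits 1, 3, 4, 5 and 6: 5 × £65 = £325.
- Doses 2 to 12: 11 × £10 = £110.
- Sum: £325 + £110 = £435.
- Remainder: £565 − £435 = £130 = 2 × £65, which fits visit 2 with its two sampling sessions. This amount is implied by the total, not stated.

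So £325 + £130 + £110 = £565, of which £455 is for visits and £110 for doses. (The list names neither visit 7 nor visit 8. That is a separate matter and leaves the £110 unchanged.)

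**2. Dose-dependent share.** £110 / £565 = 19.5%.

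**3. Amount forgone when gel is withheld.** This assumes that withheld doses are not made up later; the protocol does not describe making them up. For m withheld doses the loss is m × £10. For a permanent stop before dose k it is (13 − k) × £10.

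| Situation | Loss | Share of £565 |
|---|---|---|
| Interruption, 1 dose | £10 | 1.8% |
| Interruption, 5 doses | £50 | 8.8% |
| Permanent stop before dose 9 | £40 | 7.1% |
| Permanent stop before dose 6 | £70 | 12.4% |
| Permanent stop before dose 3 | £100 | 17.7% |
| Permanent stop before dose 2 | £110 | 19.5% |

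**4. Which reports move a grade.** From Appendix 6:

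- *Discomfort.* Grade 1 is discomfort that is easily tolerated. Grade 2 is awareness of symptoms most of the time without loss of daily activities. The line between them is subjective, and it is the line at which 9.4.1 interrupts gel.
- *Erythema.* Diffuse moderate or severe redness is grade 2 with easily tolerated discomfort and grade 3 with grade 2 discomfort. For the same observed redness, discomfort understated by one grade turns a grade 3 event into a grade 2 event. The event then leaves the grade 3 or above endpoint and the section 9.5 count, and it calls for interruption instead of discontinuation.

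**5. How often signs are checked during home dosing.** Sections 7.6 to 7.8 give two telephone calls (day of doses 2 to 4 and of doses 8 to 10) and one examination, at visit 5 (day of doses 5 to 7). The next examination is visit 6, 12 hours after dose 12. Between visits 5 and 6, symptoms reach the team through one call or if the woman makes contact.

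**The case against.** **The forfeit is inferred.** Section 16.2 gives a rate and a total for the full schedule; it does not say that withheld doses go unpaid. The participant information sheet was not available for review and may settle the matter. This stands as a limit: the point rests on 16.2 as written.

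**Grade 2 does not end dosing.** A reader might infer that one grade 2 report costs a woman all her later dose payments. Section 9.4.1 does not support that, because interruption is temporary and reversible; only 9.4.2 is permanent. The full £110 is a corner case: gel stopped for good before dose 2, by which time she has been examined with colposcopy at 1, 8 and 24 hours after dose 1. Visit payments need not be lost, since follow-up continues.

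**Much of the safety data is not self-report.** Events are solicited and looked for at repeated examination and colposcopy. Epithelial disruption and oedema are observed signs. A grade 2 symptom reported as grade 1 still counts among all adverse events. All this stands, and it keeps the point modest. It does not cover symptoms left unmentioned, bleeding between visits, or the erythema line in step 4.

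**No bias between arms.** A reader might infer that the result is tilted towards the antibody gels. The incentive is the same in all three blinded arms, so no such tilt is built in.

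**Adherence.** Section 8.7 says: "Compliance/adherence will be assessed by history and by inspection of returned syringes". A reader might therefore want payment for doses missed by choice as well, so that missed doses are admitted. That is a debatable trade-off, because paying per dose used also encourages the dosing on which the samples after dose 12 depend. The protocol's choice there is not an error.

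**Conclusion.** The point holds in a limited form. As 16.2 and 9.4 are worded, reporting a genital symptom that triggers 9.4 costs the woman £10 per withheld dose: £10 to £50 (1.8% to 8.8% of £565) for a one-to-five-dose interruption, and up to £110 (19.5%) in the extreme case of a permanent stop before dose 2. This is a modest incentive to understate discomfort and bleeding. Its likely direction is lower absolute event counts in every arm, with a possible effect on the section 9.5 halt count.

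The conclusion rests on reading the payment as due only for doses actually used, on withheld doses not being made up, and on the unseen information sheet not already saying otherwise. The protocol gives no basis for any percentage of under-reporting, so none is offered.

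**What to change.** Add one sentence to section 16.2, to this effect: *the £10 is also paid for each scheduled home dose withheld because dosing was interrupted or discontinued under section 9.4 for an adverse event, provided the unused syringe is returned.* Check the information sheet and align it.

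Leave section 9.4 as it stands, leave doses missed by choice as they are, and keep the £565 for a completer.

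The condition on syringes needs no new procedure, because section 7.8 already has used and unused syringes collected at visit 6 or 7. The cost is £10 per withheld dose, at most £110 for a woman whose gel is stopped, so no woman receives more than a completer does.

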## **17. PUBLICATION**

The results of the study will be analysed and compiled in a study report and published in a peer-reviewed journal. The results and analyses will be published as soon as possible.

No verbal or written report on the primary or secondary objectives of the trial may be made without the approval of the EMPRO consortium. The CI, Trial Statistician and Principal Investigators will form the basis of the writing group.

If there are named authors on publications, these should include at least the CI and Trial Statistician. If there are no named authors (i.e. group authorship) then a writing committee will be identified that would usually include these people, at least. The ISRCTN that has been allocated to this trial should be attached to any publications resulting from this trial.

The members of the DMC should be listed with their affiliations in the Acknowledgements/Appendix of the main publication.

## **18. PROTOCOL AMENDMENTS**

Version 3.3, 29 March 2010, incorporates changes to the location of processing and storage of samples, the deletion of references to Diary Cards as source data (except for the timing of doses), deletion of reference to entry into CRF of reports from Polymun, changes to the identifiers used for samples at the pathology laboratory of York Hospital, and deletion of references to HYMS EMU as the sole location in York Hospital for volunteer visits.

Version 3.2, 8 Sept 2009, incorporates a change in the timing of the baseline participant (self)-taken vaginal aspirate from pre-dosing at visit 2 to the screening visit (visit 1) for logistical reasons.

Version 3.1, 6 July 2009, incorporates minor changes requested after formal review by the Sponsor.

Version 3.0, 9 June 2009, incorporates a number of changes which have been made as a result of changes to the schedule to extend the time window of the sampling points. In addition, a brief participant information leaflet has been added, changes to the SAE reporting procedures and adverse definitions have been made for the purposes of clarity. Other changes were made as detailed in the relevant notification of substantial amendment.

Version 2.1, 10/10/2008 was amended in line with comments received from Cambridgeshire 1 Research Ethics Committee, after review at a meeting held on the 16th September 2008. Changes consist of amendments to the Patient Information Sheet.

Version 2.0, 25/07/08 was preceded by version 1.0, 25/06/08 (submitted to the York Hospitals NHS Foundation Trust Research and Development Committee).

## **Eligibility Criteria:**

### **Inclusion criteria**

- Females
- Aged  $\geq 18$  and  $\leq 45$  years
- In good health as determined by medical history, physical examination and clinical judgement
- Willing and able to give written informed consent
- Available for the duration of the study
- Willing to undergo screening for HIV, Hepatitis B & C, and sexually transmitted infections
- Willing to abstain from vaginal practices including receptive oral sex and sexual intercourse from 48 hours before the first dose of the study gel until after visit 7
- If physiologically fertile, using a reliable method of contraception for the 3 to 4 menstrual cycles covering the pre-study, study dosing and follow up cycle to visit 8 (methods defined as one of: consistent use of condoms with every act of sexual intercourse; combined oral contraceptive pill; desogestrel-containing progesterone only pill (Cerazette); intra-uterine contraceptive device or system; injectable contraceptive; progesterone implant)
- Willing to abstain from using any genital preparations, other than the study gel, during the period of gel administration until after visit 7
- Willing to abstain from using tampons during the period of gel administration until after visit 7
- Judged by clinician to be able, and likely, to comply with the procedures required as set out in the protocol
- Have been registered with a GP for at least the past 3 months
- Response received from GP before randomisation
- Have access to a domestic refrigerator at home for the purposes of storing the study gel

### **Exclusion criteria**

- Untreated syphilis, gonorrhoea, trichomonas, chlamydia, vaginal candidosis or bacterial vaginosis
- Clinically significant (out of the normal range and deemed clinically significant by the CI or study physician) haematological, biochemical, immunological or coagulation assay abnormalities on screening
- HIV infection, anti-HCV antibody positive, HbsAg positive
- Abnormal findings on pelvic examination, deemed clinically significant by the CI or study physician
- History of coagulation or thrombotic disorders
- Significant current general medical illness
- Irregular menstrual bleeding likely to cause vaginal bleeding during the dosing period as judged by the CI or study physician
- Current participation, or participation within the last 2 months in another clinical trial
- Treatment for cervical intraepithelial neoplasia (CIN) or other gynaecological instrumentation of the cervix within the past 3 months
- Pregnant, within 12 weeks postpartum, or breast feeding
- Unlikely to comply with protocol
- Have any condition which, in the opinion of the CI or study physician, might interfere with the evaluation of the study objectives

Unable to fluently read and speak English to a level adequate for the full comprehension of procedures required in participation and consent

## Confirmation of eligibility for participation in 'Mabgel1' clinical trial

### **PATIENT IDENTIFICATION**

Surname:

\_\_\_\_\_

First Name:

\_\_\_\_\_

Date of Birth:

|  |  |  |
|--|--|--|
|  |  |  |
|--|--|--|

DAY      MONTH      YEAR

### **PATIENT HISTORY**

Is this patient currently registered with your practice?

Yes ☐      No ☐

Has this patient been registered with you for at least 3 months?

Yes ☐      No ☐

If 'no' please indicate the date of registration with your practice:

|  |  |  |
|--|--|--|
|  |  |  |
|--|--|--|

DAY      MONTH      YEAR

***If you answer 'yes' to any of the following questions, please provide details in the 'comments' section below.***

Has the patient been involved in another clinical research study within the past 2 months?

Yes ☐      No ☐

Does the patient have any history of coagulation disorders, such as vitamin K deficiency, von Willebrand's disease, haemophilia or any clotting factor deficiencies?

Yes ☐      No ☐

Does the patient have a history of any significant general medical illness?

Yes ☐      No ☐

Has the patient received treatment for cervico-epithelial neoplasia (CIN) or other gynaecological instrumentation of the cervix within the past 3 months?

Yes ☐      No ☐

Has the patient receiving any prescription medication from your practice in the last 12 months ?

Yes ☐      No ☐

Is there any reason that you feel your patient should not be entered into this study?

Yes ☐      No ☐

*Please turn over*

**Thank you.**

## **APPENDIX 5: MABGEL – STORAGE INSTRUCTIONS AND INSTRUCTIONS FOR USE**

[figure not shown][figure not shown]

### **Mabgel – Instructions for use**

#### **How should I store the gel?**

You have been provided with 11 doses of the study gel in individually packed syringes. If you think you have not been given the correct number of doses, please contact the research team immediately, using the contact details below.

As soon as you get home, please place the syringes containing the study gel in the fridge. Keep the syringes inside the plastic bag provided. Keep each dose of the study gel in the fridge and in its original packaging until you are ready to use it.

Please keep all used syringes in the extra bag provided. Do not keep this bag in the fridge.

#### **When should I use the gel?**

Dose 1 will have been applied by a nurse or doctor at the clinical unit.

Doses 2 to 11 should be applied at home, just before going to bed.

Dose 12 should be applied at home in the evening at <<enter time>>, as instructed by the study doctor or nurse.

## **How to use the gel:**

1. Wash your hands before using the study gel.
2. Remove the syringe from its outer packaging (all of the syringes are the same, so it doesn't matter which one you use first).
3. Remove the rubber stopper from the end of the syringe.
4. Place the end of the syringe into the end of the applicator and hold in place. Check that the plunger on the applicator is fully pressed down.
5. Gently push down the plunger on the syringe, bringing the gel into the cylinder of the applicator. Make sure that the plunger on the syringe is fully pressed down so that all of the gel has been transferred into the applicator.
6. Remove the syringe from the applicator.
7. While lying down, knees bent and spread apart, gently insert the cylinder of the applicator well into the vagina. Press the plunger to transfer the gel from the applicator to the vagina. Make sure that the plunger is fully pressed down before removing.
8. With the plunger still depressed, remove the applicator, holding it by the cylinder.
9. Dispose of the used applicator in the bin, but do not throw away the used syringe.
10. Place the used syringe and rubber stopper into the plastic bag provided. Return all used syringes to the clinical trial unit when you come back for your follow up appointment.
11. Wash your hands.
12. Remember to record the time that you used the gel in the diary card.

**If you have any problems using the gel or you have any other questions or concerns, contact the study team on [name] at any time.**

